# Children Immunization App (CImA) Among Syrian Refugees in Zaatari Camp, Jordan: Protocol for a Cluster Randomized Controlled Pilot Trial Intervention Study 

**DOI:** 10.2196/13557

**Published:** 2019-10-07

**Keywords:** mHealth, refugees, vaccines, Jordan, Syria

## Abstract

**Background:**

There are up to 19.4 million children who are still unvaccinated and face unnecessary deaths, especially among refugees. However, growing access to smartphones, among refugees, can be a leading factor to improve vaccination rates.

**Objective:**

This study aims to determine whether a smartphone app can improve the vaccination uptake among refugees and determine the app’s effectiveness in improving the documentation of vaccination records.

**Methods:**

We developed and planned to test an app through a cluster randomized trial that will be carried out at the Zaatari refugee camp in Jordan. The study will be open to all parents who carry Android smartphones, have at least one child, and agree to participate in the study. The parents will be recruited to the study by trained volunteers at the vaccination sites around the Zaatari camp. Inclusion criteria will be the following: having at least one child of 0 to 5 years, being a local resident of the camp, and having an Android smartphone.

**Results:**

The intervention includes an app that will allow storing Jordanian vaccination records, per child, on the parents’ smartphones in Arabic and English (in an interchangeable fashion). Every record will have a set of automated reminders before the appointment of each child. The app will summarize immunization records in form of due, taken, or overdue appointments, labeled in orange, green, and red, respectively. Baseline will include the collection of our primary and secondary outcomes that are needed for the pre and postdata measurements. This includes social demographic data, any previous vaccination history, and electronic health literacy. Participants, in both study arms, will be monitored for their follow-up visits to the clinic for vaccination doses. For the study outcome measures, we will measure any differences in the uptake of vaccinations. The secondary outcome is to analyze the effect of the children immunization app on visits for follow-up doses.

**Conclusions:**

Owing to the limited evidence of effective interventions for childhood vaccination among refugees, research in this area is greatly needed. The project will have a significant impact on the health of refugees and the public health system. In Jordan and the Middle East, the vaccination level is low. Given the influx of refugees from the area, it is crucial to ensure a high vaccination level among the children.

**International Registered Report Identifier (IRRID):**

PRR1-10.2196/13557

## Introduction

### Background

Child immunization is a key component of the World Health Organization and the United Nations Children’s Fund (UNICEF)’s child survival intervention package [1]. Immunizing children is an essential strategy in the primary health care services, and it is a crucial public health objective. However, internationally, there are up to 19.4 million children who are still unvaccinated and face unnecessary deaths [2], especially among refugees [3]. Owing to this, refugees from conflict-torn countries have a high risk of acquiring Vaccine Preventable Diseases (VPDs) [4], especially as half of the refugees are below 18 years [5]. In conflict-torn countries, such as Syria, the immunization systems and follow-up, along with information systems, have been weakened, and herd immunity has been compromised. Before the crisis, Syria had greater than 80% of immunization coverage [6], which reduced to below 50% during the period 2011 to 2015. The total number of measles cases also increased from 13 to 740 in late 2011 and early 2013 (approximately an increase of 57-fold in less than 12 months) [2]. Since 2011, over 3 million children, aged 0 to 5 years, have fled out of Syria, to the Middle East and Europe [7]. These children have been exposed to several risky situations on the way to their new hosting countries, including passing or living in countries with low vaccination coverage [6]. In 2017, Roberton et al reported that the vaccination rate among Syrian children was 25% and 13% in Jordan and Lebanon, respectively [8]. Therefore, they are at a high risk of acquiring VPDs. This causes a heightened risk of unnecessary outbreaks in host countries, particularly among individuals who have not been vaccinated at all or completed vaccination schedules, whether refugee or from the host population [9]. The estimated cost of hospitalization may be up to US $25,000 per case [10]. The influx of children without clear immunization records therefore creates a challenge for health providers to maintain herd immunity and vaccinate unvaccinated children [5,9,11,12]. At the same time, the vaccination rate in the hosting country is considered low, for example, in Jordan, the vaccination rate among the general population is estimated to be less than 50% [13]. Given the risk to unvaccinated children, both in the refugee populations and the general population, it is paramount that support is given to health professionals to monitor and increase the rate of vaccination among refugee children. The challenge for monitoring vaccinations among refugees is compounded by the use of the yellow vaccination cards, which are easily lost or not brought to medical consultations. The field of mobile Health (mHealth) could be used as an alternative for paper-based vaccination records, and a smartphone app could present advantages to empower parents by informing them of vaccination schedules and dates and allowing them to monitor vaccination coverage on their own. There is growing evidence on the effectiveness of smartphone technologies in supporting health care services [14], though there remain gaps in the evidence of effectiveness. Smartphones provide a novel approach to solve problems with data registration, transmission, and storage [15-18]. Currently, there are over 5.2 billion users, in low- and middle-income countries [19]. The number of purchased cell phones is expected to exceed the total number of people on earth [20]. The emergence and spread of smartphones have provided a novel approach toward improving access to health care services [17]. The advancement of technology has provided tools that can empower users [21], patients, and other populations at risk. In general, mHealth can be useful among the population and among vulnerable groups, such as refugees [22]. Refugees and other vulnerable populations use smartphones as a survival kit, to connect with their social networks and to search for information about their host countries [10]. Anecdotally, women are the main caregivers for their children, and they are active users of smartphone technologies, so they can stay in touch with their social network and seek information regarding the integration process in the hosting countries [23]. It is therefore possible to use technological innovations, such as apps, to develop appropriate tools to support both women and men refugees, as well as health care professionals involved in the delivery of urgent health services. Health technology innovation is playing a crucial role in helping refugees, in various contexts around the world, including low-, middle-, and high-income countries [24].

However, there remains a lack of well-conducted evaluations of mHealth interventions among refugee populations, particularly with respect to maternal and child health. According to our knowledge, no study has used an app to support refugees’ population in recording their vaccination records and provide them an automated reminder for the vaccination visits. The purpose of this study is to develop and evaluate an mHealth intervention that helps Syrian refugees to store their immunization and health records to facilitate health information sharing at the Zaatari camp in Jordan.

### Objectives

The objectives are as follows:

To implement an integrated app intervention in collaboration with UNICEF, Ministry of Health, United Nations High Commissioner for Refugees (UNHCR), and local health service delivery partnersTo analyze the uptake of vaccination coverage (primary outcome)To analyze the effect of the smartphone app intervention on visits for the follow-up doses (secondary outcome)To conduct a thorough process evaluation of the intervention implementation

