### Sample Size Calculation

The sample size was calculated using G*Power 3.1.9.2 for testing the effect of the intervention by McNemar test. For 1-tailed hypothesis, at a power of 80% and level of significance of 0.05, a sample of 374 children is needed to detect a clinically important change in the proportion of children who will come back for their follow-up doses after introducing the intervention (ie, odds ratio of 1.5) [25]. After adjusting to potential proportion of lost to follow-up, the estimated sample size becomes 535. The analysis will be performed using Stata Statistical Software: Release 14 (College Station, TX: StataCorp LP.).

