### Assessments

Baseline will include the collection of our primary and secondary outcomes that are needed for the pre and postdata measurements. This includes social demographic data, any previous vaccination history, and electronic health literacy [27]. Participants, in both study arms, will be monitored for their follow-up visits to the clinic for the vaccination doses. The vaccination cards of both study arms will be marked as *intervention* or *control* arm; thus, the clinic nurses will notify the field workers about the follow-up visits. For the study outcome measures, we will measure any differences in the proportion coming back on time for the follow-up vaccination visit. The secondary outcome is the utility of the CImA app.

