### Statistical Analysis

The analysis will be done using a set of steps. The baseline characteristics of the participants will be compared between the intervention and control groups, using independent 2-tailed *t* test for continuous variables and Chi-square test for categorical variables. Delta analysis (D%) will be used to assess the change in the vaccination rate between preintervention (t0) and postintervention (t1), contrasting this change within the intervention and control groups. This will be complemented by an effect size assessment to quantify the difference in change between the 2 groups (Cohen *d* test will be used). Hierarchical level modeling will be conducted to consider any cluster effect of the clinics (defaulters will be treated as intent-to-treat analysis in the primary outcome of the study). For the secondary outcome, survival analysis will be used to further contrast the difference in the secondary outcome (proportion of defaulters) between the intervention and comparison groups, postintervention (t1). Stata will be used for the data analysis.

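### The trial is powered on return for follow-up doses, which the Objectives call secondary, and the sections disagree on which outcome is primary

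*Protocol article*

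**What the plan says.** Five parts of the protocol article bear on this.

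- **Objectives:** the team will "analyze the uptake of vaccination coverage (primary outcome"; the next aim is the "effect of the smartphone app intervention on visits for the follow-up doses (secondary outcome".
- **Abstract (Results):** "we will measure any differences in the uptake of vaccinations", followed by "The secondary outcome is to analyze the effect of the children immunization app on visits for follow-up doses".
- **Sample Size Calculation:** a one-tailed McNemar test at 0.05 with 80% power and an odds ratio of 1.5 needs 374 children, raised to 535 for loss to follow-up. The quantity to be detected is a "change in the proportion of children who will come back for their follow-up doses".
- **Assessments:** for the study outcome measures, "we will measure any differences in the proportion coming back on time for the follow-up vaccination visit". Then: "The secondary outcome is the utility of the CImA app".
- **Statistical Analysis:** the pre-to-post change in vaccination rate comes first (delta analysis, Cohen d, then a hierarchical model for clinic effects). Survival analysis is for the "secondary outcome (proportion of defaulters".

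**The concern.** A reader who wants to know which single result decides this trial gets two answers. The Objectives and Abstract point to uptake or coverage. The sample size and Assessments point to return for the next dose. The endpoint with a stated power is the one the Objectives rank second, and the endpoint ranked first has no sample-size support in the text.

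Two things are at stake. First, the 80% power could be read as applying to the coverage result, which it does not. Second, after the data are in, the team could lead with coverage or with return and cite a section in support of either choice. A 5% error rate protects the conclusion only if the choice was fixed beforehand.

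**Working it through.** **1. The sections side by side**

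| Section | Main outcome | Secondary outcome |
|---|---|---|
| Objectives | Uptake/coverage (labelled primary) | Visits for follow-up doses |
| Abstract | Uptake of vaccinations | Visits for follow-up doses |
| Sample Size Calculation | Return for follow-up doses (the powered endpoint) | none given |
| Assessments | On-time return | App utility |
| Statistical Analysis | Change in vaccination rate (analysed first) | Proportion of defaulters |

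The Objectives, Abstract and Statistical Analysis form one group. Sample Size Calculation and Assessments depart from it. The McNemar test that sets the sample size does not appear in Statistical Analysis, and that section does not say which of its analyses decides the trial.

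**2. The plan's own sample size**

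Inputs from Sample Size Calculation: odds ratio 1.5, one-sided 0.05, power 80%. Among discordant pairs, p = 1.5/(1 + 1.5) = 0.6. By the normal approximation the discordant pairs needed are

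[(1.645 × 0.5 + 0.842 × √(0.6 × 0.4)) / (0.6 − 0.5)]² ≈ 152 (158 by the exact binomial).

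The total depends on the proportion of pairs that are discordant, which the article does not print. With π for that proportion,

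N = [(1.645 × 2.5 + 0.842 × √(2.5² − 0.5² × π)) / 0.5]² / π.

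At π = 0.41 this gives 375. The exact calculation gives 379 at π = 0.43 and 362 at π = 0.45. So 374 is attainable with a discordant proportion of about 0.41 to 0.45. Over π = 0.2 to 0.6 the exact total runs from 814 down to 271. The inflation reproduces with an assumed 30% loss: 374/0.70 = 534.3, rounded up to 535. I take the figures as attainable and raise no point about the unprinted inputs. What matters is that every input concerns return for follow-up doses.

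**3. Power for the named primary**

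Sample Size Calculation gives no baseline coverage rate and no target difference in coverage. No power for coverage can be derived from it.

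**4. Error rate if the headline is chosen late**

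Two candidates, each tested at 5%, independence assumed: 1 − 0.95² = 0.0975, about 9.8%. If the two tests agreed perfectly the rate would stay at 5%. A child who returns for a dose also adds to coverage, so the correlation should be positive and the true figure should lie between 5% and 9.8%.

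**5. Does 374 carry over to a between-arm test of return?**

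This is an illustration under assumptions: equal arms of 187, odds ratio 1.5, one-sided 0.05, clustering ignored. With n per arm and p̄ the mean of the two proportions,

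power = Φ{[p₂ − p₁ − 1.645√(2p̄(1 − p̄)/n)] / √([p₁(1 − p₁) + p₂(1 − p₂)]/n)}.

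- p₁ = 0.50, p₂ = 0.60: 62%.
- p₁ = 0.25, p₂ = 0.333: 55%.
- p₁ = 0.80, p₂ = 0.857: 43%.

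A design effect above 1 for clinics would lower these. Renaming the primary therefore does not by itself bring the stated 80% with it.

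**The case against.** The strongest reply is that the conflict is narrow. The Objectives and Abstract agree, Study Design gives raising immunization coverage as the aim, and Statistical Analysis takes vaccination rate first and defaulting second. Assessments never uses the word primary. The title calls the trial a pilot, and the Discussion promises only preliminary insight.

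Part of this stands. Statistical Analysis broadly supports the Objectives, so it would be wrong to say that every section disagrees. The pilot label softens the point but does not remove it: Study Design states an effectiveness aim, and Sample Size Calculation fixes a powered hypothesis test. Assessments sets its study outcome measures against a secondary outcome, so on-time return reads there as the main one. Even without that reading, Objectives and Sample Size Calculation still conflict.

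A reader might also infer several stronger things that the article does not support:

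- **Three competing primaries and a 14.3% error rate** (1 − 0.95³ = 0.143). Return and default overlap heavily and may be complements, though the article does not define a defaulter. They should not be counted as two independent tests alongside coverage.
- **App utility compared between arms.** Assessments does not say so. The Objectives already plan a process evaluation, where utility fits.
- **Children who do not attend clinics can never enter, so coverage is unsuitable.** Recruitment is at the clinics, but Study Design says social workers also inform camp residents. Such selection would affect return as well, so it does not decide between the two outcomes.
- **The sample size is already based on on-time return.** Sample Size Calculation refers to coming back, with no timing.

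**Conclusion.** The point holds as an internal contradiction. Coverage is the named primary, return for follow-up doses is the powered endpoint, and Assessments sides with return. The stated 80% power does not apply to the outcome the Objectives name, and the text leaves the team free to lead with either.

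The inflation in false positives is at most about 9.8% against a nominal 5%, for two candidates under independence, and less with the positive correlation expected here. The contradiction itself rests on the wording alone and needs no numerical assumption. It should be settled before anyone sees results by arm, because until then the trial's main result cannot be identified in advance.

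**What to change.** By a dated amendment, made without sight of results by arm:

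1. Name one primary outcome and the between-arm test that decides it, in the same words in the Abstract, Objectives, Sample Size Calculation, Assessments and Statistical Analysis. The hierarchical model already planned for clinic effects is an obvious choice of test.
2. Return for the next scheduled dose is the natural candidate, because it is closest to the powered endpoint and both arms are monitored for it. Define the window that counts as on time. Coverage and time to return then become secondary.
3. If coverage is kept as primary, which is equally coherent, state that the 374/535 calculation and its 80% power do not apply to it.
4. In either case restate the power for the chosen primary and its between-arm test. The present figure comes from a one-tailed paired calculation and should not be presented as supporting that comparison.
5. Report app utility descriptively, in the app arm only, within the process evaluation.

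Cost: wording in five places, a definition of on time, and a fresh power statement. No new data are needed. The drawback is that the primary label may change while enrolment is ongoing. That must be disclosed, with the date and a statement that results by arm had not been seen. The restated power may also be lower than 80%.

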## Methods

### Study Setting

The study will be conducted at the Zaatari camp in Jordan (5.3 km^2^), which is considered one of the largest hosting camps for refugees in Jordan and the Middle East. The camp was first opened in 2012, to host the Syrian refugees fleeing the Syrian civil war. The camp population is estimated to be hosting 80,000 refugees (approximately 15,000 persons per km^2^), where approximately 20% (n=16,000) of them are under 5 years.

### Study Design

This will be a cluster randomized controlled trial to evaluate the effectiveness of using an app to record the vaccination schedule, including reminders for parents, on increasing immunization coverage of Syrian children at the Zaatari refugee camp in Jordan. In March 2019, the study was announced through posters in Arabic, in the clinics. Clinicians and social workers will also inform the residents of the camps about the study. Parents interested in joining the study will be fully briefed about the study, and an informed consent form will be signed. After completing the consent form, participants (1) included in the app intervention arm (ie, children immunization app [CImA] recipients) will receive the usual care, access to the CImA app, and instructions on how to use it, in addition to updating their children vaccination card, or (2) under the usual care (control arm) of the trial, where they will receive the usual information on the benefits of vaccination, the child’s yellow vaccination card will be updated, in addition to the list of appointments for the future vaccines. The vaccination sites will be enrolled on the basis of convenience, because of the security situation in the refugee camp.

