## Discussion

This paper describes the study protocol for a randomized controlled trial of a smartphone app on child vaccination at one of the largest Syrian refugee camps in the world. Owing to the current gap in children vaccination coverage in Jordan, this study will provide an important preliminary insight on using a smartphone app to improve child immunization in a refugee camp, and this study will be unique in certain ways. First, according to our knowledge, this is the first cluster randomized controlled trial of a smartphone app–based intervention to support the national vaccination program. This includes the effects on the immunization coverage, follow-up visits, and the experience of both of health care staff and parents in using the app. The outcome of this study will be of high importance for the different collaborators, including UNICEF, UNHCR, and the Jordan-Ministry of Health.

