### Conclusions

Owing to the limited evidence of effective interventions for childhood vaccination among refugees, research in this area is greatly needed. The project will have a significant impact on the health of refugees and the public health system. In Jordan, and the Middle East, the vaccination level is low. Given the influx of refugees from the area, it is crucial to ensure a high vaccination level for the refugees, especially for children, to avoid VPDs.

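### The title calls the trial a pilot, but its aim and sample size are those of an effectiveness test, for which at most 7 clinics probably leave it severely underpowered

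*Protocol article*

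**What the plan says.** Two places in the protocol article present a preliminary study. The title reads "Protocol for a Cluster Randomized Controlled Pilot Trial Intervention Study", and the Discussion says "this study will provide an important preliminary insight on using a smartphone app".

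Three places present a test of effectiveness. The Abstract's Objective reads "This study aims to determine whether a smartphone app can improve the vaccination uptake among refugees". Study Design opens with "This will be a cluster randomized controlled trial to evaluate the effectiveness of using an app". Sample Size Calculation is built on "testing the effect of the intervention by McNemar test" and continues: "For 1-tailed hypothesis, at a power of 80% and level of significance of 0.05, a sample of 374 children is needed". The effect to be detected is an odds ratio of 1.5, and the total rises to 535 after allowance for loss to follow-up.

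The Objectives section has four items: implement the app with partners, analyse vaccination coverage (primary), analyse the effect on follow-up visits (secondary), and carry out a process evaluation. Recruitment is at 7 clinics (Intervention), sites are enrolled by convenience (Study Design), and Statistical Analysis plans hierarchical modelling for the effect of clinic.

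**The concern.** A pilot and an effectiveness trial permit different conclusions from the same data. A pilot estimates the quantities needed to plan a later trial, and its p-value carries no claim. An effectiveness trial is sized so that its test can carry one. With both descriptions in force, a favourable result could be reported as evidence that the app works, and an unfavourable one set aside because the study was only a pilot. How the trial is read would then depend on how it came out. That risk concerns future reporting and is not something the article says will happen. It is easiest to remove before the analysis.

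The choice of label would matter less if the design could support the stronger reading, so the precision available from at most 7 clinics has to be checked.

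**Working it through.** **The plan's own figure.** For a McNemar test, an odds ratio of 1.5 means a share of 1.5/2.5 = 0.6 among discordant pairs. Discordant pairs needed, one-sided 0.05 and 80% power: (1.645 × 0.5 + 0.842 × √(0.6 × 0.4))² / (0.6 − 0.5)² ≈ 152.5. The article does not give the discordant proportion, so 374 cannot be strictly reproduced. It is consistent with a proportion of 152.5/374 ≈ 0.41. The step to 535 implies 30% loss: 374/0.70 = 534.3, rounded up. This is a pre-post figure for one group. It has no control arm and no cluster term.

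**Target as a between-arm difference.** This reads the odds ratio of 1.5 as an effect between arms, which is an assumption.
- From 50%: odds 1 × 1.5 = 1.5, so 60%, a gain of 10 points.
- From 25%: odds 0.333 × 1.5 = 0.5, so 33.3%, a gain of about 8 points.

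**Interval width with clinics as the randomised unit.** From the article: 535 children and 7 clinics, so 535/7 = 76.4 per clinic. Assumed: 3 versus 4 clinics, 50% returning, ICC 0.01, 0.02 or 0.05.
- Variance of a clinic proportion = 0.25 × (ICC + (1 − ICC)/76.4).
- SE of the difference = √(variance × (1/3 + 1/4)).
- Half-width = 2.571 × SE (t on 5 df).

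| ICC | Variance | SE | Half-width (points) |
|---|---|---|---|
| 0 | 0.0033 | 0.044 | 11.2 |
| 0.01 | 0.0057 | 0.058 | 14.9 |
| 0.02 | 0.0082 | 0.069 | 17.8 |
| 0.05 | 0.0156 | 0.095 | 24.5 |

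At ICC 0.02, an observed gain of 10 points would have an interval from about −8 to +28.

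**Sensitivity.**
- With 25% returning, the half-widths at ICC 0.01, 0.02 and 0.05 are 12.9, 15.4 and 21.2 points, against a target of about 8.
- With 374 analysed children, the number left after the planned loss, they are 16.6, 19.2 and 25.6 points at 50%.

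**Power for a two-arm odds ratio of 1.5.**
- Ignoring clustering, 80% one-sided power needs 734, 610 or 788 children in total for control proportions of 25%, 50% or 70%. The minimum over all control proportions is about 606, above both 374 and 535.
- With 7 clinics split 4 versus 3 (noncentral t, 5 df, design effect 1 + (m − 1) × ICC, where m is the number of children per clinic, control 25% to 70%), one-sided power at ICC 0 is 43–51% with 374 children and 54–63% with 535. At ICC 0.01 to 0.05 it is about 19–45% across the two sizes.

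**Can significance be reached at all?** With 4 versus 3 clinics there are 35 allocations. The smallest permutation p-value is 1/35 = 0.029 one-sided and 2/35 = 0.057 two-sided.

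**The case against.** The best defence is that this is a matter of labelling. Two of the four objectives concern implementation and process evaluation, Assessments names the utility of the app as a secondary outcome, and the Discussion mentions the experience of staff and parents. These are ordinary pilot interests, so a reader who infers that the objectives contain nothing of a pilot would be wrong. Some planning quantities will also come out of the analysis: Assessments measures on-time return, and hierarchical modelling will yield between-clinic variation. How such outputs feed a later trial may be set out in the full protocol, which is not shown. All of this stands. It does not remove the conflict, because the primary outcome and the sample size are about effect and the stated aims do not name these quantities as planning inputs.

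The precision figures rest on assumptions. The article names the clinic only as a cluster level in the analysis. If arms were mixed within clinics, the half-width at 50% would be about 1.96 × √(0.25 × 4/535) = 8.5 points, or 10.1 with 374 children. Use of the baseline measurement could narrow the interval, while loss to follow-up would widen it. This stands too, and it limits how firmly the size can be stated.

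Two stronger readings are tempting. One is that the design is incapable of supporting a significant result. The permutation count shows that a one-sided p below 0.05 is attainable, so the defect is low power. The other is that the sentence in the Conclusions, "The project will have a significant impact on the health of refugees and the public health system", announces the result in advance. In context it is a general statement about the value of the project, and the point does not rely on it.

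**Conclusion.** The point holds as an unreconciled framing. The title and the Discussion describe a pilot, while the Abstract's Objective, Study Design and Sample Size Calculation describe a powered test of effectiveness. Nothing in the article says which governs the conclusion.

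On the natural reading that clinics are randomised, the between-arm interval of about ±15 to ±25 points is wider than the 10-point target, and the trial is severely underpowered for an effectiveness claim. That range assumes a 3 versus 4 split, about 50% returning and an ICC of 0.01 to 0.05. The shortfall against 80% power needs no ICC: even with no clustering, neither 374 nor 535 children suffice for a two-arm odds ratio of 1.5. That result still depends on reading the odds ratio as a between-arm effect.

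**What to change.** Make the aims match the title. In the Abstract's Objective, the Objectives section and Study Design, state that this pilot will estimate on-time return by arm, the cluster-adjusted between-arm difference with its 95% confidence interval, the between-clinic ICC, and retention. State also that no claim of effectiveness will rest on its p-value.

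If the sponsor wants an effectiveness trial instead, remove the word pilot and restate the power in Sample Size Calculation for a two-arm comparison with clustering and few clusters. The intervals shown here come from assumed inputs and cannot stand in for that calculation. The sentences on impact in the Conclusions need no change.

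The first option requires rewording and no new data. Its costs are that the sponsor gives up a confirmatory claim, and that the objective is reworded while enrolment is ongoing, so the change should be dated and explained.
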